**Figure 1 F1:**
[figure not shown]
**Study Flow Chart**.

As an inducement to study enrollment, we will allow crossover after the primary outcome data have been collected at six weeks. Participants may crossover to the other blinded treatment arm if they believe they had insufficient benefit from the first two injections. Also at six weeks, patients will return to discuss potential crossover and to again have blood drawn for cortisol, HbA1c and fasting glucose measures. Those who choose not to crossover at six weeks will be allowed to have one additional injection of the same type as originally assigned at the nine-week time point, if they desire. After nine weeks, patients and physicians will be allowed to make treatment decisions per usual care. This may include ESIs or other treatments as determined by the patient and physician.

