### Analytic approach

We are utilizing "intent-to-treat" [24] analyses for the primary effectiveness evaluation, which evaluates outcomes based on the treatment arm to which individuals are assigned. Crossover is not allowed until after the outcome measures have been collected at the study primary endpoint of 6 weeks; therefore, the primary results will reflect the treatment to which the participant was randomized. The evaluable patient subset is defined as those patients with data available for analysis based on their initially randomized treatment. Consideration of missing data is essential to characterize the potential for selection bias through attrition. Characteristics of patients with missing follow-up data will be compared to those with complete data. In sensitivity analyses, we will impute missing outcome data in multiple ways to assess its impact on the primary analyses.

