### Secondary analyses

We will conduct two subgroup analyses to assess evidence for treatment effect on the primary outcome measures within categories defined by race and injection approach (transforaminal/interlaminar). We do not hypothesize that the treatment effect will be larger or smaller in one subgroup compared to another, only that there is a significant treatment effect within each subgroup.

We will assess secondary outcomes using ANCOVA models for continuous measures and logistic regression models for binary measures. These analyses will include assessment of group differences in clinically meaningful changes in pain and function (e.g., at least a 30% improvement on the Roland Morris Disability Questionnaire and pain scores).

Secondary analyses will consider the complete time profile for the primary outcome measures of pain and function through 12 months using methods appropriate for the analysis of repeated measures. Crossover and missing data will complicate analysis of follow-up data. Long-term outcomes will be evaluated using linear mixed effects models for repeated measures in both intent-to-treat and as-treated analyses. We will tabulate crossover rates by randomized treatment arm and compare the rates using Chi-squared tests and logistic regression as appropriate. To assess the impact of crossover on the overall evaluation of ESI, we will examine longitudinal models of outcome that incorporate a time-varying covariate indicating when treatment occurred.

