### Economic outcome measures

The economic evaluation will include an assessment of health care utilization, costs, and cost-effectiveness for the steroid group compared to those receiving local anesthetic alone in the intention-to-treat sample. The co-primary economic outcomes will be incremental per participant average costs compared to per participant Roland Morris Disability Questionnaire improvement and incremental cost per quality-adjusted life year (QALY) gained from both a payer and societal perspective [25]. The QALY will be calculated using the EQ-5D, a standardized health outcome instrument used to estimate "utility weights" for cost-utility analysis http://www.euroqol.org. We will estimate incremental cost-effectiveness ratios for six weeks, six months and one year using advanced sensitivity analyses to adjust parameter ranges for uncertainty in clinical, cost, or effectiveness variables [26]. The impact of complications and adverse effects on resource utilization and costs will be summarized for both groups.

The primary economic research question is whether treatment with steroid combined with anesthetic will be safer and more effective than treatment with local anesthetic alone, at a differential cost within willingness-to-pay thresholds of U.S. payers, using an incremental cost per QALY gained approach. The one-year societal perspective analysis will include direct and indirect costs, using standardized payer-based reimbursement amounts (i.e., unit costs). In summarizing overall costs, we will include costs reported by participants via resource use questionnaires, in addition to the sum of estimated reimbursed amounts associated with care used. Within-health-system resource utilization will be assessed using clinical, pharmacy and administrative data from the participating health plans' electronic systems. We will use the health plan data to assess medical utilization events (e.g., office visits, surgeries, tests) and the pharmacy data to assess filled prescriptions. Average unit prices for resource use (pharmacy and medical) will be applied to participants' health system utilization using a reimbursement database containing payer expenditures within each health system. These unit cost estimates (i.e., payer reimbursement amounts) will come from an independent, private insurance claims data warehouse, i.e., Marketscan^® ^[27].

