The effectiveness measures for the cost-effectiveness analysis will be obtained directly from the primary statistical analysis. The cost-effectiveness assessment will use a decision-tree framework to quantitatively assess the costs and effects for the randomized groups. Short-term cost-effectiveness outcomes will use the intention-to-treat approach, while longer-term, one-year outcomes will use empirical approaches to estimate EQ-5D and Roland Morris Disability Questionnaire outcomes in relation to cost. The assessment will allow for different resource use patterns and test ranges of assumptions for treatments and procedures. Empirical data from LESS and from external sources which included the relevant outcome measures [28,29] will be used to estimate the expected effects and costs for ESI-randomized participants, modeling outcomes of Roland Morris Disability Questionnaire and EQ-5D at three, six, and 12 months. These data will be used to model treatment groups under the assumption that no crossover occurs at the six-week endpoint and participants do not deviate from their randomized treatment during the 12-month study, rather than modeling diverse crossover treatment patterns and associated outcomes for participants, which will be presented descriptively. Data on improvement or decrement in outcomes will be used to estimate the trajectory of Roland Morris Disability Questionnaire or EQ-5D for treatment groups. Presenting ranges of cost-effectiveness estimates using different approaches will allow for a "triangulation" of results to assess consistency, so that payers and policy makers can have comprehensive information for decision-making. The analysis will be influenced by published data on treatment patterns and guidelines, in addition to assessing trends in Marketscan^® ^data during several years. Costs will be estimated in 2013 US$, the year the study will conclude. As is standard practice in cost-effectiveness analyses of 12 months or less, no discounting of costs or effects will be performed for the 12-month study. Sensitivity analyses will be conducted by testing a 20% range versus base case values for cost parameters and effectiveness measures, as well as using probabilistic sensitivity analysis approaches [26]. Additional testing will be performed on cost-effectiveness parameters having the greatest impact on the variability of cost-effectiveness estimates.

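### Patients choose crossover because of poor response, so the as-treated and time-varying long-term estimates are at risk of confounding; the one-year economic analysis is described both as intention-to-treat and as a no-crossover model

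*Protocol article*

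**What the plan says.** Study design (text after Figure 1) sets the switching rule: "Participants may crossover to the other blinded treatment arm if they believe they had insufficient benefit from the first two injections". For the others, "Those who choose not to crossover at six weeks will be allowed to have one additional injection of the same type as originally assigned", at nine weeks. Then "After nine weeks, patients and physicians will be allowed to make treatment decisions per usual care", which may include further ESIs.

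Analytic approach protects the primary endpoint: "Crossover is not allowed until after the outcome measures have been collected at the study primary endpoint of 6 weeks".

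Secondary analyses evaluates long-term outcomes with "linear mixed effects models for repeated measures in both intent-to-treat and as-treated analyses". To assess the impact of crossover, "we will examine longitudinal models of outcome that incorporate a time-varying covariate indicating when treatment occurred". Crossover rates are to be tabulated and compared by arm, and the text concedes that crossover complicates follow-up. It does not say how as-treated is coded, which analysis leads, or how selection into crossover is handled.

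Economic outcome measures describes cost-effectiveness "for the steroid group compared to those receiving local anesthetic alone in the intention-to-treat sample", with ratios at six weeks, six months and one year. Later in the same section ITT is kept for short-term outcomes, and the one-year groups are modelled "under the assumption that no crossover occurs at the six-week endpoint and participants do not deviate from their randomized treatment during the 12-month study". Cost per Roland-Morris improvement is listed as a co-primary economic outcome and again under the secondary economic question.

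**The concern.** Switching depends on the patient's own response. Control patients who do well stay put, while those who do badly move to steroid. If exposure means having received ESI, the unexposed group is left with mainly good responders, and ESI looks harmful even when it does nothing. A mixed model does not remove this by itself; the result depends on the coding and on which scores are in the model.

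This matters because the ITT contrast weakens as crossover rises, so readers will look to the as-treated and no-crossover results for the one-year answer, and these have the least protection. The Discussion also promises high-quality one-year data. On the economic side, two descriptions of the same one-year ratio leave open which comparison a payer will be shown.

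**Working it through.** **1. The plan's own figure.** From Sample size: 400 patients, 85% follow-up, SD 7.5, baseline correlation 0.3, difference 2.25, two-sided α = 0.05.
- Per arm: 400 × 0.85 / 2 = 170
- Adjusted SD: 7.5 × √(1 − 0.3²) = 7.155
- SE: 7.155 × √(2/170) = 0.776
- Power: Φ(2.25/0.776 − 1.96) = Φ(0.939) = 82.6%

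This agrees with the stated 83%. The figure is not in dispute; 2.25 points serves as the yardstick below.

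**2. Bias of an *ever ESI* indicator on post-crossover scores.** Assumptions, not in the protocol:
- no true effect at six weeks or later
- crossover q = 0.41 in each arm, by a logistic rule on the six-week score with slope 0.5 to 1.5 per SD
- within-person correlation ρ = 0.5 to 0.7
- no baseline adjustment

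Let m be the mean standardised six-week score of those who do not cross; it is negative.
- Unexposed (control non-crossers): mean m
- Exposed (whole ESI arm, mean 0, plus control crossers, mean −m(1 − q)/q): mean −m(1 − q)/(1 + q)
- Gap: 2|m|/(1 + q)
- Bias: 7.5 × ρ × 2|m|/(1 + q)

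Numerical integration of the logistic rule over a standard normal score gives |m| = 0.194 at slope 0.5 and 0.437 at slope 1.5.
- Low end: 7.5 × 0.5 × 2 × 0.194 / 1.41 = 1.03 points
- High end: 7.5 × 0.7 × 2 × 0.437 / 1.41 = 3.25 points

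Simulated variants of this setting run from 1.0 to 3.4. A sharper rule (the worst 20% or 40% cross, with noise) gives 1.7 to 4.4, adjusted for baseline.

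**3. How coding and model change the answer** (simulation, no true late effect, positive = against ESI):

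| Analysis | Bias, RMDQ points |
|---|---|
| ITT | about 0 |
| Ever ESI, post-crossover scores only | 1.0 to 3.4 |
| Ever ESI, six-week score kept as a response, crossover driven by that score | about 0 |
| Same model, crossover driven by a latent state | 0.5 to 1.5 (2.3 to 2.8 under the sharper rule) |
| Current treatment, symmetric crossover | about 0 |
| Current treatment, six-week score omitted, crossover unequal because of a 2.25-point six-week effect (sharper rule) | 0.2 to 0.6 |

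Entering the six-week score as a covariate is not equivalent to keeping it as a response. With a 2.25-point six-week effect and no late effect, covariate adjustment left 0.2 to 1.3 points of bias, depending on coding.

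**4. Dilution of ITT.** Suppose the late effect is 2.25 and belongs wholly to current treatment. Simulated crossover was 16% (ESI) and 24% (control) at 20% overall, and 34% and 46% at 40% overall.
- 20% overall: 2.25 × (1 − 0.16 − 0.24) = 1.35
- 40% overall: 2.25 × (1 − 0.34 − 0.46) = 0.45

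The simulated values agree (1.36 and about 0.44).

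**5. The economic text, side by side.**
- Analysis set: the opening of the section gives the ITT sample, with ratios up to one year. The later text gives ITT for the short term and a no-crossover model for one year, with actual crossover patterns only described.
- Source of effects: effectiveness is to come directly from the primary statistical analysis, which reports six-week outcomes. The one-year effects are modelled from trial and external data.
- Rank of cost per Roland-Morris improvement: co-primary in one place, under the secondary question in another.

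**The case against.** The strongest reply has four parts.

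First, a reader might infer that the trial's one-year effects are confounded. The protocol does not support that: an ITT long-term analysis is planned, and the six-week primary result is collected before any crossover. This stands in full.

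Second, the large bias needs both *ever ESI* coding and omission of the six-week score. The protocol states neither and speaks of the complete time profile through 12 months. Under that reading the bias can vanish. This stands in part: the trigger is the patient's belief about benefit, not the recorded score, and the bias returns if that belief tracks more than the score captures. The text fixes neither the coding nor the scores used.

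Third, a reader might infer that the one-year cost per QALY is confounded, or that the no-crossover model covers one arm only. Neither is shown. It is a decision-tree model fed by trial and external data, with several approaches compared and sensitivity analyses planned. One sentence names only participants randomised to ESI, but the surrounding sentences refer to both treatment groups. The model is open to confounding; no more can be said. Varying inputs by 20% would not correct selection, however, and the conflict over the analysis set remains.

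Fourth, adjustment methods may sit in an analysis plan that is not shown, so their absence is weak evidence. True, but the point rests on what is stated: a response-driven switching rule, unranked methods that as described do not deal with it, and two conflicting accounts of the economic analysis.

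**Conclusion.** The concern holds in a limited form. The long-term as-treated and time-varying estimates are not randomised comparisons and are at risk of confounding by poor response. The possible bias runs from about 0 to 3.4 Roland-Morris points against ESI under moderate selection, and to more under sharper selection, so it can exceed the 2.25-point design difference. That range rests on assumed crossover rates, selection strengths and correlations; the protocol gives none of these. The six-week result and the ITT one-year contrast are not confounded, but the ITT contrast may be heavily diluted. The economic inconsistencies, in analysis set and in rank, stand on the text alone and need no assumptions. These are secondary and economic analyses, and the changes are cheap enough to be worth making.

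**What to change.** 1. Name the ITT contrast at 3, 6 and 12 months as the main long-term result.
2. Label the as-treated and time-varying analyses exploratory and define the exposure coding. Keep the three- and six-week scores in the model as responses, and adjust for selection into crossover. One way is inverse-probability weighting on baseline, three- and six-week RMDQ and pain scores, treatment guess and treatment preference. This does not handle usual-care ESIs after week nine unless later outcomes and treatments are modelled too.
3. Reconcile the two economic descriptions: make the comparison by randomised arm the one-year base case, and the no-crossover model a scenario applied to both arms alike. Participant-reported resource use covers four three-week windows (12 of 52 weeks), so modelling is still needed for the other weeks.
4. Give cost per Roland-Morris improvement one rank.

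The cost is wording and extra analysis; the adjustment variables listed are already collected. The weighted estimates will have wider intervals, and the leading one-year effect will be the diluted ITT one, which the report should say.

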### Economic outcome measures

The economic evaluation will include an assessment of health care utilization, costs, and cost-effectiveness for the steroid group compared to those receiving local anesthetic alone in the intention-to-treat sample. The co-primary economic outcomes will be incremental per participant average costs compared to per participant Roland Morris Disability Questionnaire improvement and incremental cost per quality-adjusted life year (QALY) gained from both a payer and societal perspective [25]. The QALY will be calculated using the EQ-5D, a standardized health outcome instrument used to estimate "utility weights" for cost-utility analysis http://www.euroqol.org. We will estimate incremental cost-effectiveness ratios for six weeks, six months and one year using advanced sensitivity analyses to adjust parameter ranges for uncertainty in clinical, cost, or effectiveness variables [26]. The impact of complications and adverse effects on resource utilization and costs will be summarized for both groups.

The primary economic research question is whether treatment with steroid combined with anesthetic will be safer and more effective than treatment with local anesthetic alone, at a differential cost within willingness-to-pay thresholds of U.S. payers, using an incremental cost per QALY gained approach. The one-year societal perspective analysis will include direct and indirect costs, using standardized payer-based reimbursement amounts (i.e., unit costs). In summarizing overall costs, we will include costs reported by participants via resource use questionnaires, in addition to the sum of estimated reimbursed amounts associated with care used. Within-health-system resource utilization will be assessed using clinical, pharmacy and administrative data from the participating health plans' electronic systems. We will use the health plan data to assess medical utilization events (e.g., office visits, surgeries, tests) and the pharmacy data to assess filled prescriptions. Average unit prices for resource use (pharmacy and medical) will be applied to participants' health system utilization using a reimbursement database containing payer expenditures within each health system. These unit cost estimates (i.e., payer reimbursement amounts) will come from an independent, private insurance claims data warehouse, i.e., Marketscan^® ^[27].

The secondary economic question is whether steroid injections represent good value for money as evidenced by non-QALY incremental cost-effectiveness ratios (i.e., cost per improvement in back-related functioning and cost per improvement in back pain, using Roland Morris Disability Questionnaire and other pain/function measures). Other consequences (outcomes) will be described in relation to cost or use profiles (e.g., ranges of the Roland Morris Disability Questionnaire, pain numeric rating scale measures, categories of medication use, imaging or other diagnostic testing, and other provider use). Marketscan^® ^data will be used for unit cost estimates.

During four, three-week time periods over the course of the twelve month study (weeks: 1-3, 4-6, 24-26, and 50-52), participants will complete Resource Utilization Questionnaires to record information related to out-of-pocket (out-of-system) costs, time related to seeking back pain treatment, daily use of prescription and over-the-counter medication use, and additional back therapies, along with use or purchases of other back-care products. We will describe the participant-reported data by randomized groups. Additional descriptive analyses will include assessing treatment group differences in dis-aggregated EQ-5D items representing activities of daily living (mobility, self-care, usual activities, pain/discomfort, anxiety/depression).

The effectiveness measures for the cost-effectiveness analysis will be obtained directly from the primary statistical analysis. The cost-effectiveness assessment will use a decision-tree framework to quantitatively assess the costs and effects for the randomized groups. Short-term cost-effectiveness outcomes will use the intention-to-treat approach, while longer-term, one-year outcomes will use empirical approaches to estimate EQ-5D and Roland Morris Disability Questionnaire outcomes in relation to cost. The assessment will allow for different resource use patterns and test ranges of assumptions for treatments and procedures. Empirical data from LESS and from external sources which included the relevant outcome measures [28,29] will be used to estimate the expected effects and costs for ESI-randomized participants, modeling outcomes of Roland Morris Disability Questionnaire and EQ-5D at three, six, and 12 months. These data will be used to model treatment groups under the assumption that no crossover occurs at the six-week endpoint and participants do not deviate from their randomized treatment during the 12-month study, rather than modeling diverse crossover treatment patterns and associated outcomes for participants, which will be presented descriptively. Data on improvement or decrement in outcomes will be used to estimate the trajectory of Roland Morris Disability Questionnaire or EQ-5D for treatment groups. Presenting ranges of cost-effectiveness estimates using different approaches will allow for a "triangulation" of results to assess consistency, so that payers and policy makers can have comprehensive information for decision-making. The analysis will be influenced by published data on treatment patterns and guidelines, in addition to assessing trends in Marketscan^® ^data during several years. Costs will be estimated in 2013 US$, the year the study will conclude. As is standard practice in cost-effectiveness analyses of 12 months or less, no discounting of costs or effects will be performed for the 12-month study. Sensitivity analyses will be conducted by testing a 20% range versus base case values for cost parameters and effectiveness measures, as well as using probabilistic sensitivity analysis approaches [26]. Additional testing will be performed on cost-effectiveness parameters having the greatest impact on the variability of cost-effectiveness estimates.

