A few cohort studies suggest that ESI may provide short-term pain relief [7,8]. However, the results of RCTs have been less favorable. One early RCT [9] demonstrated no advantage of ESI over saline or local anesthetic injections. However, some argue that the poor results of this trial were a consequence of inadequate technique and do not reflect the current practice of performing ESI with fluoroscopic guidance to ensure appropriate placement of the steroid medication [10].

Only one RCT of fluoroscopically-guided ESI compared to injections with local anesthetic alone has been published [11]. This study, while showing improvement in each group, found no advantage of the steroid injection over an injection of local anesthetic alone [11]. However, this study suffered significant methodological limitations including lack of statistical power, no primary outcome measure, un-blinding of patients and researchers and a high dropout rate (21/60 patients).

The overall objective of this multi-center, double-blind RCT is to evaluate the effectiveness of ESI plus local anesthetic versus local anesthetic alone in improving pain and function among older adults with back pain and lumbar spinal stenosis. We hypothesize that patients randomized to receive ESI with local anesthetic will show significantly greater improvement in pain and function compared to patients randomized to receive local anesthetic only. We will also examine whether ESI is differentially effective in improving pain and function for different patient subgroups (African-Americans vs. Caucasians and patients undergoing a transforaminal vs. interlaminar approach). Finally, we will compare resource use and costs in the two treatment groups as well as incremental cost-effectiveness and incremental cost utility from both payer and societal perspectives.

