## Discussion

As there has been scant research focusing on ESI in older adults with pain due to spinal stenosis, little is known about treatment risks and benefits for this population. Although it has been demonstrated that surgery can be effective for severe spinal stenosis, there are many elderly patients for whom surgery carries substantial risk. There is a need for safer, less-invasive treatment options for older adults with the hope of reducing functional disability and promoting independence. Although ESI is a promising treatment alternative and is widely used in clinical practice, its effectiveness is unknown. Compared to young and middle-age adults, a much higher percentage of older adults have co-morbid conditions such as diabetes that may increase the risks due to systemic absorption of corticosteroids.

As in most clinical trials, we anticipate that recruitment may be a challenge. Patients suffering from pain may be reluctant to delay what they might consider to be definitive therapy. We have developed strategies to increase our chances of successful recruitment including the use of a patient-education video, which was a successful strategy in our prior trials [29]. We have multiple clinical recruitment sites and have added additional clinical sites to attain our recruitment targets. We also have included an optional crossover design to maximize our ability to recruit patients with severe pain into the trial.

The results of this study should provide compelling evidence as to whether or not epidural steroid injections are effective in improving function and pain in the elderly with lumbar spinal stenosis. The LESS trial will provide high-quality data for shorter-term outcomes (six weeks) and longer-term (one-year) outcomes. The patient-reported outcomes, the electronic medical and pharmacy utilization records, and supporting economic data providing reimbursed amounts for resources used will enable a robust evaluation of the comparative benefits and harms associated with epidural steroid injections with anesthetic versus local anesthetic alone.

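### The longer-term economic model names outside data for the steroid arm only, which cannot be squared with the statements that its effects come from the randomised comparison

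*Protocol article*

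**What the plan says.** All of the following is in the Protocol article, under Economic outcome measures unless stated.

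- The section opens by comparing the steroid group with participants "compared to those receiving local anesthetic alone in the intention-to-treat sample". It promises incremental ratios at six weeks, six months and one year. Cost per Roland-Morris improvement and cost per QALY are the co-primary economic outcomes.
- On the source of the effects: "The effectiveness measures for the cost-effectiveness analysis will be obtained directly from the primary statistical analysis". Under Primary analyses, that analysis reports six-week outcomes of randomised participants.
- Short-term results are to follow intention to treat. One-year results are to use what the text calls empirical approaches.
- The inputs for 3, 6 and 12 months are trial data together with "external sources which included the relevant outcome measures [28,29] will be used to estimate the expected effects and costs for ESI-randomized participants" (references 28 and 29).
- The next sentence reads: "These data will be used to model treatment groups under the assumption that no crossover occurs at the six-week endpoint". A later one says that data on improvement or worsening "will be used to estimate the trajectory of Roland Morris Disability Questionnaire or EQ-5D for treatment groups".
- Planned safeguards are a comparison of several approaches, a 20% range around base-case values, and probabilistic sensitivity analysis.

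The only other mention of either reference is in the Discussion, which cites "the use of a patient-education video, which was a successful strategy in our prior trials [29", with the citation number at the end. Reference 28 is described nowhere beyond having the relevant outcome measures.

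**The concern.** An incremental cost-effectiveness estimate from a randomised trial is credible because both arms come from the same randomised population. If one arm's expected outcome or cost is partly taken from other studies, any difference in population, treatment or calendar time between those studies and this trial enters the increment and is reported as an effect of steroid. This is separate from crossover: even if crossover were handled perfectly, outside data in one arm would make the contrast partly non-randomised.

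The outputs at stake are the six-month and one-year cost per Roland-Morris improvement and cost per QALY, which the section offers to payers and policy makers.

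**Working it through.** **1. Set the statements side by side.**

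| Statement | What it implies for the longer-term increment |
|---|---|
| Evaluation "compared to those receiving local anesthetic alone in the intention-to-treat sample" | Both arms as randomised, trial data |
| "The effectiveness measures for the cost-effectiveness analysis will be obtained directly from the primary statistical analysis" | Trial data, but that analysis is at six weeks |
| "Empirical data from LESS and from external sources which included the relevant outcome measures", applied to steroid-assigned participants | Trial plus outside data; steroid arm named, control arm not |
| "These data will be used to model treatment groups under the assumption that no crossover occurs at the six-week endpoint" | The same data applied to groups in the plural; the control arm's source is still unstated |

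The first two rows cannot both describe an estimate built as in the third. The fourth leaves open whether the control arm also receives outside data, and on what terms. The six-month ratio is also unplaced. The departure from intention to treat is stated for one-year outcomes, yet the modelled time points include three and six months.

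**2. Are outside data needed to fill gaps?** Under Baseline and follow up assessments, Roland-Morris and EQ-5D are collected at 3, 6 and 12 months. Resource questionnaires cover weeks 1-3, 4-6, 24-26 and 50-52, and health-system records supply utilization. A trial-only comparison by assigned arm is therefore feasible.

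**3. How a mixed input moves the increment.** The plan gives no weight and no external value, so there is no planned figure to reproduce and the bias itself cannot be computed. Let S and C be the trial's own expected outcomes for steroid and control. Let w be the weight on outside data in the steroid arm, and b the amount by which the outside-based value differs from S. Then

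increment = (1 - w)S + w(S + b) - C = (S - C) + w·b.

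The shift is w·b. If the control arm also receives outside data, with weight v and discrepancy d, the shift is w·b - v·d. It vanishes only when the two products are equal.

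**4. Illustration on assumed values (Roland-Morris points).**

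| w | b = 0.5 | b = 1 | b = 2 |
|---|---|---|---|
| 0.25 | 0.125 | 0.25 | 0.5 |
| 0.50 | 0.25 | 0.5 | 1.0 |
| 0.75 | 0.375 | 0.75 | 1.5 |

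For scale only, the Sample size section powers the six-week comparison for 2.25 points: 0.125/2.25 = 6% and 1.5/2.25 = 67%. That benchmark is internally sound. With 200 × 0.85 = 170 per arm and SD 7.5 × √(1 - 0.3²) = 7.15, power is 82.6% against the stated 83%. It is a six-week design difference and not a one-year economic quantity.

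**5. Would the 20% range reveal it?** The range is centred on a base case that already contains w·b. Suppose the trial-only increment were 2.25, the shift +1.5, and the range applied to the increment. The base case is then 3.75 and the range 0.8 × 3.75 = 3.0 to 1.2 × 3.75 = 4.5, which misses 2.25. With a shift of +0.125 the range is 1.9 to 2.85, which includes it. So the range can cover a small shift but neither detects nor corrects a large one. Probabilistic analysis spreads parameter uncertainty around the same centre.

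**The case against.** **One-arm use is not settled.** A reader might infer from the one sentence that outside data certainly enter the steroid arm alone. The text does not establish this, because the following sentences refer to groups in the plural. If both arms were shifted equally, the bias would cancel. This stands as a limit on the finding. It does not rescue the plan, because symmetric use is nowhere stated and cancellation depends on it.

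**Nothing shows that references 28 and 29 are unsuitable.** A reader might infer from the Background that they do not test this comparison. That section says "Only one RCT of fluoroscopically-guided ESI compared to injections with local anesthetic alone has been published [11" (reference 11) and cites reference 9 for an earlier trial, but it never mentions 28 or 29. It follows that they are not those two trials. Their population, treatment and comparator are not given, so the documents do not support saying more. Nor does the text say that having the right outcome measures was the reason for choosing them.

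**Safeguards exist.** Short-term results stay intention to treat. The Secondary analyses section plans long-term mixed models on trial data, both intention to treat and as treated. Several economic approaches will be compared. This stands in part. However, no trial-only longer-term economic estimate is named among those approaches, and none is designated as the base case.

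**The no-crossover target is a legitimate choice.** Crossover is allowed from six weeks, so a comparison by assigned arm answers a different question, about strategies that include crossover. This stands, and is why the model should be kept and labelled.

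**Input detail may sit in a fuller economic plan.** That is fair for the exact weights. It does not explain statements within one section that disagree about where the effects come from.

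**Conclusion.** The concern holds in limited form. The section gives statements about the source of longer-term effects that do not agree. Its literal wording puts outside data into the steroid arm's effects and costs without a matching control input. On that reading the increments at 3, 6 and 12 months are not purely randomised contrasts, and the planned sensitivity analyses would not correct this.

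The size and direction of any bias are unknown. The range of about 0.1 to 1.5 Roland-Morris points rests wholly on the assumed weights (0.25 to 0.75) and differences (0.5 to 2 points), and on one-arm use. It shows the mechanism and is not an estimate; under identical shifts in both arms it would be zero.

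The six-week primary effectiveness analysis and the short-term economic results are untouched. This should be corrected, but it does not threaten the trial's main conclusion.

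**What to change.** 1. Reconcile the statements within Economic outcome measures: say which outputs use the intention-to-treat sample, which use the primary analysis, and which use outside data, and place the six-month ratio explicitly.
2. Name as the reference estimate the trial-only comparison of costs, Roland-Morris and EQ-5D by assigned arm at six months and one year.
3. Keep the no-crossover model that uses references 28 and 29 as a separately labelled scenario, with a sentence on their populations and comparators.
4. State that any outside input is applied symmetrically to both arms, so that the increment itself comes from randomised trial data.

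The cost is rewording; no new data are needed. The downside is that the trial-only one-year estimate is less precise and describes strategies that include crossover. Symmetric use of an outside trajectory also carries its own assumption about how the treatment difference persists after six weeks, which should be stated with the scenario.
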